## Abstract

**Background:**

Even effective interventions for people with dementia and their caregivers require specific implementation efforts. A pilot study showed that the highly effective community occupational therapy in dementia (COTiD) program was not implemented optimally due to various barriers. To decrease these barriers and make implementation of the program more effective a combined implementation (CI) strategy was developed. In our study we will compare the effectiveness of this CI strategy with the usual educational (ED) strategy.

**Methods:**

In this cluster randomized, single-blinded, controlled trial, each cluster consists of at least two occupational therapists, a manager, and a physician working at Dutch healthcare organizations that deliver community occupational therapy. Forty-five clusters, stratified by healthcare setting (nursing home, hospital, mental health service), have been allocated randomly to either the intervention group (CI strategy) or the control group (ED strategy). The study population consists of the professionals included in each cluster and community-dwelling people with dementia and their caregivers. The primary outcome measures are the use of community OT, the adherence of OTs to the COTiD program, and the cost effectiveness of implementing the COTiD program in outpatient care. Secondary outcome measures are patient and caregiver outcomes and knowledge of managers, physicians and OTs about the COTiD program.

**Discussion:**

Implementation research is fairly new in the field of occupational therapy, making this a unique study. This study does not only evaluate the effects of the CI-strategy on professionals, but also the effects of professionals' degree of implementation on client and caregiver outcomes.

**Clinical trials registration:**

NCT01117285

## Background

Dementia is associated with a major decrease in quality of life of clients and their caregivers due to a loss of independence, autonomy, and social participation [1]. In addition, dementia is a major driver of costs in health care [2]. These costs increased by 34% between 2005 and 2009 [3]. In the Netherlands, nearly 1% of people aged 65 years old suffer from dementia and 40% of people aged 90 and over [4]. The number of dementia patients will increase substantially in the years to come [5]. This stresses the importance of effective interventions which aim at increasing quality of life of people with dementia and their caregivers [6] and implementation of these interventions in practice.

Two recent pilot studies showed that strategies currently used to implement the COTiD program are not effective ([name] & [name]: Pilot research to the implementation by trained OTs of the COTiD program, unpublished)

([name], [name], [name], [name], [name], [name]: Implementing of an effective occupational therapy guideline for older persons with dementia and their informal caregivers: facilitating and impeding factors, submitted). It was evaluated if a post-graduate course on working with community occupational therapy in dementia (COTiD) program was sufficient in establishing implementation in practice ([name] & [name], unpublished). Although the COTiD program was proven to be an effective [7] and cost effective intervention [8], only 20% ([name] & [name], unpublished) of the trained OTs used the program completely or partly due to existing barriers ([name] et al, submitted). These findings are in agreement with previous studies reporting on the ineffectiveness of post-graduate courses and workshops with regard to the use of new knowledge in practice [9-11].

To make sure patients with dementia and their caregivers are able to receive and benefit from occupational therapy according to the COTiD program, a combined implementation (CI) strategy was developed addressing the existing barriers to implementation ([name] et al, submitted). A multifaceted strategy was created as previous studies found this to be most effective in changing professional's behavior [9,12,13]. The combined implementation (CI) strategy exists of various strategies intended to improve OTs' adherence to the COTiD program, increase community OT use, and to increase managers' and physicians' knowledge and attitudes regarding the COTiD program.

The current study aims to compare the effectiveness of the CI-strategy with the effectiveness of the usual educational (ED) strategy in increasing both OTs adherence to the COTiD program and the use of community OT. In addition, the cost-effectiveness of the CI-strategy is compared to the cost-effectiveness of the ED-strategy. In this article, the design of this cluster randomized trial is described according to the latest CONSORT guidelines of randomized controlled trials on non-pharmacological interventions [14].

## Methods/Design

### Trial Design

A single blinded, cluster randomized controlled design is used to compare the effectiveness and cost-effectiveness of the two implementation strategies. An independent statistician stratified the clusters by type of setting (hospital, nursing home, and mental health services) and randomized them to either the control (educational strategy) or experimental group (the combined implementation strategy) (see Figure 1). Clusters were randomized using a 2 to 1 (control vs. experimental) ratio, as it is expected that physicians in the experimental group will refer more clients for this community occupational therapy intervention than those in the control group. This assumption implies that more clusters are needed in the control group to collect data from a sufficient number of client-caregiver couples. At the time of randomization 45 organizations agreed to participate in the study.

**Figure 1 F1:**
[figure not shown]
Flow Chart of the Study Design.

Three research assistants blinded for group allocation collected all data. Client-caregiver couples are not aware of the group allocation of their healthcare professionals (physician and occupational therapist). A complete double blinded trial is not possible as the participating professionals are aware of the implementation strategy they received.

### Participants

#### Healthcare professionals

A cluster consists of occupational therapists, managers, and physicians working at a healthcare setting which delivers community occupational therapy (outpatient service general hospital, outpatient treatment from nursing home & outpatient community mental health services). Clusters were preferably formed out of professionals working at the same organization. However, in several cases professionals from different organizations formed a cluster as these were the usual networks in current clinical practice. Clusters were approached between January and December of 2009 and asked to participate in the study.

Eligibility criteria for clusters:

1. Clusters consist of at least two OTs, one physician, and one manager

2. Outpatient occupational therapy treatment is provided by the cluster

3. Each cluster is able to include at least 8 client-caregiver couples in the study

4. OTs within a cluster completed the post-graduate course on the COTiD program before the start of the study.

#### Client-caregiver couples

Clients with dementia and their caregiver are enrolled during the first year of the study. They are approached to participate in the study by physicians of one of the study clusters.

Eligibility criteria for client-caregiver couples:

1. The client has mild to moderate dementia (MMSE score 10-24, DSM IV criteria for dementia)

2. Clients are referred to an occupational therapist participating in the study

3. The client lives at home at the time of inclusion

4. The informal caregiver takes care of the client at least two times a week

5. The client is not diagnosed with depression (Geriatric Depression Scale 30 >12)

6. The client has no severe behavioral or psychological symptoms (BPSD)

7. The client has no severe illness preventing participation

8. The caregiver has no severe illness preventing participation

9. Both client and caregiver consent to participate

Participation of client-caregiver couples is discontinued when severe BPSD develops, the client is permanently admitted to an institution, or the client or caregiver no longer wish to participate.

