### Statistical methods

Random effects regression models will be used to evaluate differences in adherence and in use of community OT between the experimental and control group. Baseline scores will be used as covariates and type of setting and OT will be used as random factors.

Differences in knowledge between professionals (occupational therapists, physicians, and managers) in the experimental and control group will be evaluated using t-tests, unless data have a substantially skew distribution in which case non-parametric tests are used. Random effect regression models for repeated measures will be used to evaluate differences in knowledge at different times of measurement within each group and between groups. The influence of several characteristics of the professionals on their knowledge level will be evaluated using ANOVA (e.g. sex) and linear regression (e.g. age, years of professional experience).

Random effects regression models will be used for analyses of covariance of the outcome measures (AMPS process [23], IDDD performance [24], DQOL [25], SCQ [26], EQ-5 D [27] at 6 and 12 months (see Table 2)) based on an intention-to-treat analysis of all available data. Treatment differences between baseline and 6 months and baseline and 12 months will be computed by analysis of covariance, with age, sex, relation to patient, and baseline scores on the co-morbidity, MMSE scores, GDS scores, and outcome variable at baseline as covariates.

For all tests significance will be tested using two-sided tests with an alpha level of.05.

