### Economic evaluation

One of the primary questions of this study concerns the difference in cost-effectiveness between the CI-strategy and the ED-strategy strategy regarding adherence of OTs to the COTiD program. Secondary, the study is designed to evaluate the difference in cost-effectiveness between the implementation strategies with regard to the quality of life of clients with dementia and their caregiver. To evaluate these questions an economic evaluation will be executed from a societal viewpoint. This implies that both costs within and outside the healthcare system, are included in the evaluations [28,29].

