**Development & execution***			
Post-graduate course - developmental & execution costs			
Implementation training - developmental & execution costs			
Regional meetings - developmental & execution costs			
Coaching on the job - developmental & execution costs			
Web-based system - developmental costs			
COTiD-program website - developmental costs			
Newsletters - preparation costs			
Motivational phone calls - preparation & execution costs			

T0 = baseline measure; T1 = 6 month follow-up measure; T2 = 12 month follow-up measure/* All development and execution costs are registered throughout the entire study period.

Healthcare costs made by client-caregiver couples are collected using the Lite version of the resource utilization in dementia instrument (RUD Lite) [30]. The RUD Lite is used every 3 months during a one year period. Data on both the caregiver and client are provided by the informal caregiver. Caregivers are asked to provide information about the preceding month as retrieving information over a longer period is often unreliable. An algorithm will be used to get a reliable estimate for the total period of three months. If available, market prices are used to calculate costs. If these are not available standard cost-prices are used as identified in the Dutch manual for costs in economic evaluations [31].

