#### Cost-effectiveness and cost-utility analysis

In order to evaluate the cost-effectiveness of the two implementation strategies regarding OT adherence to the COTiD program, incremental cost-effectiveness ratios are determined expressed as cost per extra percentage adherence.

The cost-utility with regard to the treatment effects of the two implementation strategies is evaluated by determining incremental cost-utility ratios. These are expressed as cost per patient quality adjusted life year (QALY) gained and cost per caregiver QALY gained. QALYs are calculated using the scores on the EQ-5 D [27]. The EQ-5 D scores are converted to QALYs using the EQ-5 D health tariffs for the Dutch population [32].

For both analyses parametric uncertainty is handled by presenting acceptability curves resulting from bootstrap replications on the original sample. Deterministic uncertainty is covered by sensitivity analyses on the range of extremes of uncertain parameters [28].

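### Ending couples' participation at severe BPSD or permanent admission cuts off later costs, caregiver outcomes and EQ-5D, which may bias the secondary couple comparisons and the cost-utility analysis

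*Protocol article*

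**What the plan says.** The eligibility text under Client-caregiver couples closes with a stopping rule: "Participation of client-caregiver couples is discontinued when severe BPSD develops, the client is permanently admitted to an institution". The same sentence adds the wish of client or caregiver to stop. Residence at home is required only at entry: "The client lives at home at the time of inclusion". Admission is therefore something that happens after enrolment, not an eligibility matter.

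Statistical methods plans random effects models for AMPS, IDDD, DQOL, SCQ and EQ-5D at 6 and 12 months, "based on an intention-to-treat analysis of all available data". Under Economic evaluation, "an economic evaluation will be executed from a societal viewpoint", and "both costs within and outside the healthcare system, are included in the evaluations". Under Costs, "The RUD Lite is used every 3 months during a one year period", and "Data on both the caregiver and client are provided by the informal caregiver". The section on cost-effectiveness and cost-utility expresses its second result as "cost per patient quality adjusted life year (QALY) gained and cost per caregiver QALY gained", with QALYs taken from the EQ-5D.

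**The concern.** The rule ends participation in the study, not a treatment. The randomised strategies are delivered to professionals, and the two deterioration events stand in one list with withdrawal. No other section keeps such couples under observation.

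The data that stop are those the later analyses need: RUD Lite, the EQ-5D of client and caregiver, and the caregiver's SCQ, Dqol and CES-D. They stop because the client has become worse, so the missingness is likely to be informative. A random effects model fitted to all available data is valid if data are missing at random given what was observed, and that is doubtful here. Permanent admission also starts a stream of institutional costs that belongs in a societal analysis. If the combined implementation (CI) strategy changed the rate or timing of admission relative to the educational (ED) strategy, the resulting cost difference would go largely unseen.

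**Working it through.** **1. The plan's own figures.** The article gives no figure for the couple outcomes or costs. Its calculated figures, under Sample size and power calculations, concern adherence and use of community OT. Effective cluster sizes are 2/(1 + 1 × 0.05) = 1.90 and 10/(1 + 9 × 0.05) = 6.90 (article: 1.9 and 6.8). A two-sided test of two proportions at 0.05 gives 81.3% power for 57 versus 29 (20% to 50%) and 99.7% for 204 versus 102 (5% to 25%). The article states 80% and 99%. None of these inputs involves follow-up of couples, so the stopping rule leaves them untouched.

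**2. Which analyses the rule reaches.**

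| Analysis | Source of data | Affected? |
|---|---|---|
| Adherence | vignettes completed by OTs | no |
| Use of community OT | copies of referrals | no |
| Cost per percentage point of adherence | strategy costs and adherence (Table 1) | no |
| Couple outcomes at 6 and 12 months | Table 2 measures | yes, after the event |
| Cost per patient and per caregiver QALY | RUD Lite and EQ-5D (Table 2) | yes, after the event |

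**3. Illustration for permanent admission.** All rates here are assumptions. Let q be the proportion admitted within 12 months, with admissions spread evenly, so that on average 6 months per admitted client are unobserved. Uncounted institution-months per enrolled couple = 6q:

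- q = 5%: 0.3
- q = 10%: 0.6
- q = 20%: 1.2

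**4. What matters for the comparison** is the difference between arms, 6 × (q in ED − q in CI):

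- 10% versus 5%: 0.3 months per couple
- 20% versus 15%: 0.3 months
- 20% versus 10%: 0.6 months
- equal rates: 0

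**5. In cost terms.** Set home cost at 1 per month and institutional cost at k, and suppose home cost is carried forward after the event (a further assumption, which the article does not plan). The error in the between-arm cost difference is 6(k − 1) times the difference in q. For k = 2 to 4:

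- 10% versus 5%: 6 × 1 × 0.05 = 0.3 to 6 × 3 × 0.05 = 0.9 home-months per couple
- 20% versus 10%: 6 × 1 × 0.10 = 0.6 to 6 × 3 × 0.10 = 1.8 home-months per couple
- equal rates, timing and post-event costs: about zero

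No similar calculation is possible for severe BPSD, for QALYs or for SCQ, because nothing in the article bears on post-event values.

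**The case against.** **Only secondary analyses are touched.** This is right. The article itself ranks the quality-of-life economic question second.

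**Missing-data handling may be in an analysis plan that is not shown.** It may, but the rule that stops collection is stated here, and no analysis recovers costs and scores that were never collected.

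**Institutional care could be costed at standard prices from the time of admission.** The Costs section allows standard prices, and the study must learn of an admission to apply the rule. However, the article does not say that the date will be recorded or such costing done, and it would not supply caregiver time, SCQ or EQ-5D.

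Four stronger readings are tempting, and the article does not support them:

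- *The analysis is not intention-to-treat.* Data before the event are kept, and the text openly limits itself to available data. The fault is likely informative missingness.
- *Observation stops because of an outcome.* Neither admission nor BPSD is an outcome in Table 2. They are post-enrolment events that may be related to the outcomes.
- *Institutional care is excluded altogether.* Only permanent admission triggers the rule, so temporary stays are not cut off by it.
- *CI clusters will lose frailer, costlier couples.* Trial Design expects more referrals in that arm, not frailer clients. A case-mix difference would also be a recruitment bias that longer follow-up does not cure.

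**Conclusion.** The point holds for the secondary client-caregiver outcomes and the cost-utility analysis. A stated rule stops data collection on deterioration, and this sits badly with the planned 6- and 12-month comparisons and the societal viewpoint. Bias arises if event rates, timing or post-event values differ by arm. Its size and direction cannot be derived from the article, and the figures above only show how the error scales under assumed rates.

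A reader might infer that costs are understated by some 5 to 23%. That range comes from 1 − 1/(1 + 0.5q(k − 1)) with assumed q of 10 to 20% and k of 2 to 4, again with home cost carried forward. It describes the mean cost level within an arm. The incremental ratio depends on the between-arm difference, whose error can be zero at the same q. The range should not be cited as the size of the problem.

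**What to change.** Reword the stopping rule under Client-caregiver couples so that severe BPSD and permanent admission do not end data collection. While consent remains, and until death:

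- continue the caregiver-reported RUD Lite every 3 months;
- continue the caregiver measures (EQ-5D, SCQ, Dqol, CES-D) at 6 and 12 months;
- record the date of permanent admission and cost institutional days from it;
- collect the client's own self-report measures only where feasible;
- add a sensitivity analysis for informative dropout, by arm.

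If follow-up has already closed, report the number and timing of these discontinuations by arm and run the same sensitivity analysis.

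The cost is a change of wording and a small extra burden on affected caregivers. The caregiver's reporting for both covers RUD Lite only. The client's EQ-5D and Dqol are listed under the client with no proxy version stated, so some patient QALY data will stay missing. The ethics exemption rested on the questionnaires not being too burdensome, which is a further reason to limit client assessments to what is feasible. The change concerns data collection only, not clinical management.

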### Interventions

#### The Educational Strategy

Occupational therapists, physicians, and managers do not receive any intervention during the study period. Occupational therapists only received the basic three-day post-graduate course before the start of the study. This course provides background and theory on the COTiD program, and is mainly focused on skill training. Skills are trained by role-playing and homework assignments that involve video-taping actual OT sessions. In addition, OTs are asked to complete reading assignment between class meetings. The experimental strategy is offered to the control group after completion of the study.

#### The Combined Implementation Strategy

The CI-strategy is a multifaceted strategy that, beside the post-graduate course for OTs, consists of additional interventions toward occupational therapists and interventions toward physicians and managers:

*1. Implementation training days*. The training days focus on refreshing and/or increasing professional skills regarding execution of the COTiD program and skills regarding promotion of the COTiD program.

*2. Coaching on the job*. Coaching sessions are held to address individual problems experienced by occupational therapists regarding the implementation of the COTiD program. Between five and seven coaching sessions are scheduled depending on the OTs individual needs.

*3. Regional meetings*. These meetings are provided to create an opportunity for OTs to discuss practice issues with OT colleagues from the same region. Four regional meetings are organized during one year.

*4. Web-based reporting system and discussion forum*. An electronic reporting system was developed to guide OTs through the steps of the COTiD program. Treatment reports can be created for every client-caregiver couple. In addition, a link to a discussion platform is provided through which OTs are able to share experiences and exchange helpful resources.

*5. Website and newsletters*. Information on the COTiD program, its effectiveness, and cost-effectiveness is provided to physicians, managers, and OTs. The information is presented through a website and four newsletters. Information is adjusted for each group of professionals, to meet the specific needs of the group.

*6. Telephone calls*. Managers and physicians are contacted by phone at least once to evaluate if they have questions on the COTiD program and the implementation in practice. The goal is to provide more insight in the COTiD program and to motivate managers to facilitate the program and motivate physicians to refer clients to treatment according to the COTiD program. The ultimate goal is to increase the number of referrals to community OT.

Two OTs who are experienced teachers, have extensive experience in using the COTiD program, and are trained in motivational interviewing provide the implementation training, coaching, and organize the regional meetings.

The elements of the CI-strategy are selected to meet the barriers found during the pilot study ([name] et al, submitted). To meet the need for feedback and guidance expressed by occupational therapists in the pilot study ([name] et al., submitted) the two training days and coaching on the job were included. Guidance and structure in using the COTiD program is also offered by providing access to the web-based reporting system. The training days and the regional meetings are opportunities to meet colleagues and create a network, which can be used for guidance and feedback both during and after the intervention.

Both managers and physicians are part of the organizational structure in healthcare. They have an important role in the facilitation of occupational therapy. Managers of occupational therapy services need to facilitate the conditions to be able to offer OT according to the COTiD program. Physicians are needed to get eligible clients referred to occupational therapy services. However, one of the pilot studies found that managers and physicians had a lack of knowledge about the COTiD program or even occupational therapy in general ([name] et al., submitted). Therefore, strategies focused on these professionals such as the educational website, newsletters, and personal phone calls were included in the CI strategy.

The interventions toward managers and physicians have an educational nature. Although educational strategies are only slightly effective in changing behavior [15], acquiring knowledge is essential before making a decision to change behavior or not [16]. Beside the educational interventions managers and physicians are motivated during the phone calls.

